## Abstract

**Background:**

Identifying and addressing heavy drinking represents a major public health priority worldwide. Whilst the majority of alcohol screening and brief intervention (ASBI) research has been conducted in western, high-income countries, evidence is growing that ASBI can also impact positively on heavy drinkers in low- and middle-income country populations. This mixed methods study aims to assess the feasibility of conducting a fully randomised controlled trial of the effectiveness of ASBI in primary care in Kazakhstan and explore the feasibility and acceptability of implementing ASBI in this setting from patients’ and physicians’ perspectives.

**Methods:**

Six primary health care units in the region of Pavlodar will be cluster randomised to either an intervention (WHO manualised 5 min alcohol brief intervention plus alcohol leaflet) or control group (simple feedback plus alcohol leaflet). Primary feasibility measures will be rates of participation at baseline and retention of eligible patients at the 3-month follow-up point. Patient/physician questionnaires and physician focus groups will assess additional dimensions of feasibility, as well as acceptability, according to the RE-AIM framework: Reach (rates of eligible patients screened/received advice); Effectiveness (change in AUDIT-C score); Adoption (rate/representativeness of participating physicians); Implementation (quality of ASBI/barriers and facilitators to delivery); and Maintenance (potential sustainability of intervention).

**Discussion:**

This is the first trial of the feasibility and acceptability of ASBI in Kazakhstan. As the planning and assessment of implementation determinants is based on the RE-AIM framework, the project outcomes will be relevant for the future development, tailoring and implementation of ASBI in Kazakhstan.

**Trial registration:**

DRKS, DRKS00015882, Registered 17 December 2018.

## Background

Alcohol is a leading global risk factor for premature death and disability, and causally related to over 60 different medical conditions, including liver cirrhosis, cancer and cardiovascular disease [1–4]. Alcohol harm contributes to health inequalities, with a larger impact on younger age groups, mainly due to the increased risk of injuries, and higher alcohol attributable mortality rates for men compared to women [2, 5, 6]. Epidemiological data also confirm the greater alcohol-related disease burden experienced by socio-economically deprived and marginalised people [2, 7, 8]. Importantly, alcohol is a cause of significant harm to others, resulting in negative social and economic consequences, which extend beyond the individual drinker to their families, local communities and society as a whole [9–15]. As such, identifying and addressing heavy drinking represents a major public health priority worldwide [16, 17].

Globally, alcohol dependence is the most common substance use disorder; however, the prevalence of alcohol harm varies considerably across different populations [1]. In Central Asia, Kazakhstan displays particularly high levels of consumption; 7.7 L of alcohol per capita compared to 2.7 in Uzbekistan for example [18]. However, it remains challenging to determine the extent of excessive drinking in Kazakhstan due to lack of reliable data. Official statistics for 2010 suggest that 1.43% of the Kazakh population were drinking at dependent levels [19]. Yet, the World Health Organization (WHO) estimate the rate to be almost four times higher (5.2%) for the same year [20]. As in other former Soviet states, high levels of unrecorded alcohol production potentially contribute to this discrepancy. Within Kazakhstan itself, rates of alcohol consumption also vary, with the highest levels found in the Northern, Eastern and Central regions. In the Pavlodar region for example, the official prevalence of alcohol dependence in 2010 was about twice as high as that found nationally (2.3% vs. 1.4%) [19]. Whilst this difference has declined in recent years (0.75% vs. 0.61% in 2017) [21], Pavlodar continues to experience substantial alcohol-related harms, with higher rates of severe alcohol intoxications and mortality due to alcohol intoxication than the rest of the country. Compared to Kazakhstan as a whole, Pavlodar also reports a higher prevalence of hypertensive heart disease (six times higher), cardiac ischemia (23% higher), and trauma (61% higher). The mortality rate due to trauma, intoxication and accidents was found to be 30% higher in Pavlodar compared to the national average in 2016, with the number of deaths per capita caused by circulatory system diseases, 20% higher [22].

Primary health care (PHC) provides an ideal context for the early detection and secondary prevention of alcohol-related problems, due to its high contact exposure to the population [23] and the frequency with which excessive drinkers present to clinicians [24]. There is a particularly robust evidence for the delivery of alcohol screening and brief interventions (ASBI) in PHC, where patients tend to present with less acute symptoms, return regularly for follow-up appointments [25] and often build long-term relationships with their health care provider [26]. ASBI comprises two key elements. First, screening a patient to help identify those individuals drinking in a potentially hazardous or harmful way, with consistently good performance reported for both the Alcohol Use Disorder Identification Test (AUDIT) and its shorter consumption-focussed version (AUDIT-C) [27]. AUDIT was the first screening tool designed specifically to detect hazardous and harmful drinking in both primary and secondary care. Developed by the WHO AUDIT has ten questions that consider drinking frequency and intensity (binge drinking), together with experience of alcohol-related problems and dependence. At a score of eight or more out of a possible 40, its ability to detect genuine excessive drinkers (sensitivity) and to exclude false cases (specificity) is 92% and 94%, respectively. Thus, AUDIT is a highly accurate tool which has been validated in a large number of countries with consistently strong psychometric performance. It is now regarded as the ‘gold standard’ screening tool to detect hazardous and harmful drinking in primary care patients. A meta-analysis confirmed that the AUDIT-C is almost as accurate as the full AUDIT for detecting unhealthy alcohol use in adults [28]. Second, delivery of a brief behavioural intervention, designed to promote awareness of the negative effects of drinking and to motivate change [29, 30]. Across a series of systematic reviews, it has been consistently reported that brief alcohol interventions result in reduced weekly alcohol consumption [31] alcohol-related problems [32], healthcare utilisation [33] and mortality outcomes [34].

Despite this evidence, which is endorsed by the WHO [35] and embedded in clinical guidelines in Europe, Australasia and the USA [36–39], delivery of brief alcohol advice across global health systems remains low [40–42]. Moreover, even in countries where ASBI initiatives have been implemented, there has been limited evaluation of either their impact on overall delivery rates, particularly over the longer term, or to understand the mechanisms of change by which such improvements have been achieved. As a result, little is known about how and when effective ASBI interventions are implemented successfully in routine health care. In order to bridge this evidence to practice translation gap, a better understanding of the processes influencing how such health innovations and interventions are both taken up and sustained in practice is key. Further, whilst the majority of research has been conducted in western, developed countries, there is a growing body of evidence which suggests that ASBI can also impact positively on heavy drinkers in low- and middle-income country populations [43–45]. However, given the challenges experienced to date in achieving widespread implementation of alcohol interventions in countries where such preventative measures are already more established [46, 47], efforts to extend ASBI into novel settings must consider potential barriers and facilitators to effective adoption from the outset.

Standardised alcohol screening and brief interventions are not regularly implemented in PHC settings in Kazakhstan at present. Patients are asked about their alcohol consumption at health checks and receive advice as appropriate to help reduce their drinking. Where a potential alcohol use disorder is suspected, patients can be referred to specialised units for treatment. However, validated alcohol screening tools are not currently used, and the alcohol advice provided is not based on evidence-based guidelines. This protocol describes the rationale, methods and analysis plan for a pilot cluster randomised trial with embedded qualitative process evaluation that will explore the feasibility, acceptability and potential impact of implementing evidence-based ASBI in routine primary health care in Kazakhstan.

## Methods/design

### Aim

The primary aim of this study is to assess the feasibility of a proposed fully cluster randomised controlled trial of the effectiveness of ASBI in primary health care in Kazakhstan. The secondary aim is to explore the feasibility and acceptability of implementing ASBI in this setting from the perspective of patients and physicians.

Specific objectives are as follows:
To conduct a two-arm pilot feasibility cluster randomised controlled trial (cRCT) (with randomization at the level of PHCU) to assess the feasibility of a future definitive cRCT of ASBI in primary care in Kazakhstan;To explore the feasibility and acceptability of ASBI and trial processes to physicians and patients;To identify key determinants of ASBI implementation from the perspective of physicians and patients to identify specific facilitators and barriers to ASBI delivery in PHC;To estimate the parameters for the design of a definitive cRCT of ASBI in primary care in Kazahkstan, including rates of eligibility, consent, participation and retention.

### Design

This pilot trial will use a two-arm cluster randomised design with embedded qualitative process evaluation to explore feasibility and acceptability in six PHC units (PHCU) in Kazakhstan. Stratified randomization with computer-generated random numbers will be used to allocate three PHCUs to the intervention and three PHCUs to the control group, with stratification based on an initial baseline assessment of the mean number of patient visits per PHCU per day.

#### Study duration

The study started in August 2018. The anticipated study duration is 15 months in total and expected to end in November 2019. This includes a 2-month site preparation phase following ethical approval from the Medical University of Almaty, 6-month recruitment period and follow-up assessments for each patient conducted 3 months after the patient was recruited (baseline). Introduction of the study and provider training sessions were conducted in April and May 2019. Patient recruitment started in April 2019. Figure 1 describes the study process in detail.

**Fig. 1 Fig1:**
[figure not shown]
Consort flow-chart including cluster-randomised trial design. ^a^Shortened Alcohol and Alcohol Problems Perception Questionnaire

### Setting

The study will be carried out at six PHCUs in the Kazakh region of Pavlodar. All five PHCUs located in the city of Pavlodar and one PHCU the city of Aksu (region of Pavlodar), located about 40 km south of the city of Pavlodar. The list of participating PHCUs is provided in the trial register at www.drks.de.

The risk of contamination between intervention and control group is low, as every PHCU has its own catchment area and patients are only allowed to change their PHCU once a year between October and November. Furthermore, all participating physicians will be instructed to inquire whether a patient has already undergone screening in the same or any other PHCU, in order to prevent multiple screening and study contamination.

### Characteristics of participants

As a secondary preventative measure, an objective of ASBI is the early identification of individuals with hazardous or harmful alcohol use, followed by the delivery of a brief behavioural intervention to those in need of support to prevent the development of alcohol-related problems, including dependent drinking, in the longer term. This target group, by definition, is usually not seeking treatment for existing alcohol problems. However, individuals with hazardous or harmful drinking are likely to visit PHCUs for consultation on other health issues, which may be both related and/or unrelated to their drinking. Therefore, all patients with an appointment in one of the participating PHCUs are eligible for recruitment. Specific inclusion criteria are that participants must be aged between 18 and 69 years, able to follow the study procedures and have provided written informed consent. Patients with diagnosed lifetime alcohol dependency according to ICD-10 criteria will be excluded.

### Study processes

#### Recruitment

In both study arms, physicians will recruit patients presenting at routine care appointments. Patients potentially fulfilling the inclusion criteria will be informed about the study purpose and asked to take part. Each eligible patient who provides informed consent for study participation will be screened by a PHC physician for hazardous or harmful alcohol use using the three question Alcohol Use Disorder Identification Test – Consumption questionnaire (AUDIT-C) [48]. A show-card featuring the AUDIT-C questions and response options as well as illustrations of standard drink examples will be used as a visual aid for the screened patients. Additionally, all patients will be asked the remaining seven questions of the full AUDIT questionnaire in order to analyse correlations between AUDIT-C and full AUDIT scores [49]. The target population of the study consists of all PHC patients with risky, hazardous or harmful drinking, defined by an AUDIT-C score of four points or more for women and five points or more or for men. A full AUDIT score of 20 points or higher indicates a potential severe alcohol use disorder (AUD). If this is indicated and with the respective patient’s consent, these patients will be referred to a psychiatrist or narcologist for diagnostic assessment and treatment.

#### Intervention arm

In the intervention arm, patients with an AUDIT-C score of three or lower for females and four or lower for males will receive short verbal feedback based on their alcohol consumption and be given a patient information leaflet reinforcing the benefits of low-risk alcohol use. Patients with an AUDIT-C score of four or more for women and five or more or for men will receive a brief (5 min) face-to-face alcohol intervention delivered by a trained PHC physician, plus a patient information leaflet with recommendations on low-risk alcohol use. The intervention will be informed by motivational interviewing principles and structured around the FRAMES model (**F**eedback—provide feedback on the patient’s risk for harm; **R**esponsibility—the individual is responsible for change; **A**dvice—advise reduction or give explicit direction to change; **M**enu—provide a variety of options for change; **E**mpathy—take a warm, reflective and understanding approach; and **S**elf-efficacy—encourage optimism about changing behaviour) [50]. The advice will include extended personalised feedback aimed at increasing patient awareness about their drinking habits and related consequences and to enhance self-efficacy to change their drinking behaviour. In each PHCU, physicians will be provided with a 3-h training and a 1-h-booster session based on the WHO Europe ASBI training package, which has been previously adopted in Russia [51], and is comparable in content and length to the approach found to be effective in the European ODHIN trial [52]. Training will be delivered by local research staff experienced in using Motivational Interviewing techniques and in providing training to health professionals. Interactive activities and role play will be used during training sessions to build physician’s knowledge of/attitudes towards alcohol and alcohol-related harm, improve their understanding of key ASBI principles and components and boost physicians’ skills/capacity to implement ASBI in routine practice. A questionnaire will be administered to participants before and after training sessions to assess changes in knowledge, attitudes and self-rated work skills in relation in delivering ASBI in routine practice. Participants will also be asked to rate their satisfaction with the quality of training.

#### Control arm

PHC physicians in the control arm will be introduced to the study purpose, trained in the screening procedures with AUDIT-C and AUDIT including a respective booster session. All patients in the control arm will receive simple feedback, including information about their individual AUDIT-C/AUDIT score and the associated alcohol risk level, as well as a patient leaflet with recommendations for low-risk alcohol use to ensure a minimal standardised intervention.

### Data collection

#### Pre- and post-training

Provider experience, alcohol-related skills and attitudes to alcohol will be assessed prior to baseline using the Shortened Alcohol and Alcohol Problems Perception Questionnaire (SAAPPQ) [53]. Assessment of providers’ training needs will be based on the WHO training evaluation questionnaire which assesses, amongst other areas, work and training experience, knowledge of alcohol-related issues, and confidence in dealing with alcohol-related situations [51]. All physicians who decline to participate in the study will be asked to provide their work and training experience, as well as their reasons for not taking part.

#### Baseline assessments

Patient measures at baseline will be collected by case-report forms (CRF) and include socio-demographic characteristics (age, gender, ethnicity); knowledge of alcohol as an attributable factor for cancer, hypertension and liver disease; alcohol use screening score (AUDIT-C, AUDIT); and physician’s impression of drinking behaviour. Patient measures at follow-up (3 months post-baseline) will include alcohol use screening score (AUDIT-C); physician’s impression of drinking behaviour; patients’ view on the interventions received; patients’ acceptance of low-risk drinking recommendations; and patients’ view on relevance of the intervention (i.e. importance of information provided). In order to assess intervention reach, the socio-demographic characteristics of non-participating patients will also be documented.

#### Follow-up assessments

At the end of the recruitment period, participating physicians will be asked to provide their views on the implementation and potential maintenance of ASBI using structured questionnaires which will be administered by local research staff. The outcomes will inform qualitative focus groups (Table 1), which willl last approximately 60 to 90 min and will be moderated by an experienced researcher from the national study team. A semi-structured topic guide will be developed to focus discussions, drawing on key themes emerging from the structured questionnaire findings and the three major areas of interest—quality and consistency of ASBI delivered, barriers/facilitators to implementation of ASBI in PHC and the long-term sustainability of ASBI in this setting.

**Table 1 Tab1:** Key outcome measures including domains of the RE-AIM framework [54]

Dimension	Outcome measures	Assessment tool and evaluation method
Feasibility	- *Rate of eligibility*: percentage of eligible participants recruited	Case-report form; descriptive statistics
	- *Participation and retention at 3 months follow-up*: percentage of enrolled participants retained at 3 months	
Reach	- *Proportion of patients screened at baseline* Numerator: Total number of completed screens Denominator: Total number of all patients eligible for screening	
	- *Proportion of consulting patients intervened at baseline* Numerator: Total number of screen-positive patients receiving advice Denominator: Total number of patients screened positive	
Effectiveness	- *Change in AUDIT-C* score between baseline and follow-up amongst patients with risky, hazardous or harmful drinking	
Adoption	- *Proportion of staff invited that participated* Numerator: Total number of participating physicians Denominator: Total number of primary care physicians invited	
	- *Description and representativeness of staff who delivered* the screening and advice (PHC provider level)	
Implementation	- *Quality and consistency of the delivery of ASBI* given (PHC provider level; patient level) measured by quantitative interviews, provider focus groups	Provider questionnaire; provider focus groups; descriptive statistics and qualitative data analyses (content and narrative analyses)
	- *Implementation determinants* (barriers, facilitators) of ASBI delivery (PHC provider, Patient level) collected by quantitative interviews, provider focus groups	
	- *Cost of intervention*: Average time spent in minutes per patient for screening and for brief intervention.	
Maintenance	- *Potential extent to which the intervention package becomes institutionalised* (PHC provider level; patient level) collected by quantitative interviews, provider focus groups	

#### Study outcome measures

The key outcome measures to assess feasibility will be the percentage of eligible patients recruited to the study at baseline and the retention rate of eligible patients at 3-month follow-up. Additional outcome measures to assess the feasibility and acceptability of implementing ASBI in primary care in Kazakhstan will be based on Glasgow’s RE-AIM framework for evaluating public health interventions [54]. RE-AIM consists of five dimensions (**R**each, **E**ffectiveness, **A**doption, **I**mplementation and **M**aintenance), which can be measured at the individual (patient/provider) or organisational (clinic/practice) level to help to determine the potential impact of an intervention.

Outcome measures relating to feasibility and each domain of the RE-AIM framework are detailed in Table 1.

#### Data management processes

Trial data will be collected using CRFs completed by the PHC physicians. Physicians will keep a code list of all patients who have scored AUDIT-C positive (4+ for females and 5+ for males) to ensure the anonymised matching of baseline and follow-up data. Trained local research staff will collect the anonymised data from the PHCUs and enter the data in a trial-specific database to monitor CRF delivery on a bi-weekly basis. Monitoring and query management (regular descriptive queries on central database to identify errors, outliers, missing data and any irregularities) will be carried out by national study coordinators. Original records containing any personal identifiable patient data will remain in the PHCUs.

Only physicians that provide written informed consent will be eligible to participate in the focus group interviews. Discussions will be audio-recorded, transcribed in full, with any potentially identifying details removed by the transcriber. Electronic recordings will be stored on password-protected computers for analysis and will be permanently deleted once the transcription process is completed. Data will be anonymised prior to analysis and write-up to ensure confidentiality and anonymity, i.e. participants will be identified by alpha-numeric code as opposed to a name. An anonymisation log (table) of all identifiers will be created to ensure consistency and accuracy, which will be stored separately to the interview data, and only accessible to members of the research team.

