#### Data monitoring

External trained research staff will closely monitor the progress of the trial and ensure that the trial is conducted and recorded in accordance with the study protocol via bi-weekly site visits. PHC physicians are responsible for completion of the data sets. All PHC physicians will be briefed on the data documentation protocol in the training sessions. During the study, patient CRFs will be monitored continuously and checked for completeness, implausible values and correctness. If needed, corrections or additions will be made.

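### Follow-up AUDIT-C and patients' views of the advice are recorded by physicians who know their arm, which is liable to flatter both results

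*Protocol article*

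**What the plan says.** All references are to the protocol article.

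- **Recruitment:** in both arms each consenting patient "will be screened by a PHC physician for hazardous or harmful alcohol use".
- **Intervention arm:** patients who screen positive receive a "brief (5 min) face-to-face alcohol intervention delivered by a trained PHC physician", plus a leaflet.
- **Control arm:** "PHC physicians in the control arm will be introduced to the study purpose, trained in the screening procedures with AUDIT-C and AUDIT". Their patients are told their score and risk level and receive a leaflet on low-risk drinking.
- **Baseline assessments:** this section also lists the 3-month measures. They are AUDIT-C, the physician's impression of drinking, and three patient items: view of the intervention, acceptance of the recommendations, and perceived relevance.
- **Data management processes:** "Trial data will be collected using CRFs completed by the PHC physicians". Also: "Physicians will keep a code list of all patients who have scored AUDIT-C positive", which is how baseline and follow-up records are matched.
- **Data monitoring:** "PHC physicians are responsible for completion of the data sets".
- **Statistical analysis:** the one named effectiveness test is a paired t test of AUDIT-C from baseline to follow-up within each group. No between-arm test is named.

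**The concern.** AUDIT-C is self-report, and change in AUDIT-C is the only effectiveness measure in Table 1. Acceptability to patients is part of the study's secondary aim. At 3 months both kinds of data pass through a physician of the unit that told the patient about the risk and, in the intervention arm, counselled a reduction. A patient in that position has reason to report less drinking and to speak well of the advice. A physician who knows the arm may also record favourably. Randomisation does not protect against this, and the analysis cannot remove it afterwards.

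At stake are the effectiveness and patient-acceptability readings that the pilot would pass to a definitive trial, and the outcome procedure itself if it is carried forward.

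**Working it through.** **Who does what.** The sections fit together as follows.

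1. Physicians screen in both arms (Recruitment) and deliver the advice in the intervention arm (Intervention arm).
2. They know the arm. The unit of randomisation is the PHCU (Design), and training in the brief intervention is described only for the intervention arm (Intervention arm, Control arm).
3. They complete the CRFs, hold the code list and answer for the data sets (Data management processes, Data monitoring). Nothing separates baseline from follow-up in these statements.
4. Research staff collect and enter CRFs, monitor, and administer the physicians' own questionnaires. They are not said to record patient outcomes. No blinded assessor and no self-completed patient follow-up form is described.

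The risk therefore follows from a stated choice, not from a detail that the article leaves out.

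**The plan's own figure.** Statistical analysis gives 400 screen-positive patients and 50% loss: 400 × (1 − 0.50) = 200, and 200 / 2 = 100 per group. This reproduces.

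**Illustration within an arm.** The documents give neither the size of a reporting shift nor the correlation between the two AUDIT-C scores. Assume a downward shift b of 0.05 to 0.3 SD, a correlation r of 0.5 to 0.7, equal SDs at both times, and no true change. For the paired t test with n = 100 (99 df, two-sided 5%):

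- standardised change = b / √(2(1 − r)); noncentrality = 10 × that value.
- b = 0.2, r = 0.5: 0.2 / √1 = 0.20, noncentrality 2.0.
- b = 0.2, r = 0.7: 0.2 / √0.6 = 0.258, noncentrality 2.58.

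Probability of a significant reduction:

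| b (SD) | r = 0.5 | r = 0.7 |
|---|---|---|
| 0 | 2.5% | 2.5% |
| 0.05 | 7% | 9% |
| 0.1 | 17% | 25% |
| 0.2 | 51% | 73% |
| 0.3 | 84% | 97% |

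Against the plan's target effect sizes, a 0.2 SD shift is 0.2 / 0.4 = 50% of the lower and 0.2 / 0.6 = 33% of the upper.

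**Illustration between arms.** Take a simple comparison of 100 against 100, ignoring clustering, with standard error √(2/100) = 0.141 SD. If x is the part of the shift found only in the intervention arm, the chance of a significant result in its favour is 1 − Φ(1.96 − x / 0.141).

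- x = 0 (same shift in both arms): 2.5%.
- x = 0.1: 10.5%.
- x = 0.2: 29%.

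A shared shift cancels between arms. It does not cancel in the within-group test that the plan names.

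**The case against.** Several counter-arguments have force.

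- **Control arm.** A reader might infer that control patients hear only a score, so that the pressure exists in one arm alone. Control arm says otherwise: they also get their risk level and a low-risk leaflet, and their physicians complete the CRFs too. Part of the pressure is shared, and only the difference can bias a between-arm comparison. This stands.
- **Same person.** A reader might infer that the physician who gave the advice always takes the follow-up record. No section says so. It is a strong inference, but any physician in the unit would still know the arm.
- **Patient views.** The abstract mentions patient questionnaires, and Table 1 mentions quantitative interviews for patient-level items, without naming who administers them. The CRF view items therefore cannot be called the only patient-sourced acceptability data.
- **Size.** The shift is assumed throughout, and the documents do not anchor it. This stands.
- **Pilot.** The key outcomes are recruitment and retention, and effectiveness is one of five further RE-AIM dimensions. This limits the consequence. However, Statistical analysis still claims that the sample suffices for statistically significant effectiveness results, so the effectiveness reading is not incidental.
- **Remedy.** Moving AUDIT-C to self-completion at follow-up only would mix a change of mode with the change over time in every within-group test. This is right, and it shapes the fix.

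**Conclusion.** The point holds as a risk. Physicians who know the arm record self-reported drinking and opinions of the advice at follow-up, which is liable to bias drinking downwards and opinions upwards. The pressure is probably stronger in the intervention arm, but that is a judgement and not something the article shows. The documents do not support saying that the results will be biased, or by how much. The probabilities above hold only under the assumed shifts and correlations.

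The weakness is sharpest for the planned paired t tests, where even pressure common to both arms counts in full. It does not reach the recruitment and retention outcomes by this route. It should be put right, but it does not undermine the pilot's main purpose.

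**What to change.** Use the same procedure in both arms.

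1. **View, acceptance and relevance items:** the patient completes them at follow-up on a sheet that carries only the study code. The sheet is sealed and collected at the existing bi-weekly research-staff visits. These items have no baseline value, so no mode needs matching.
2. **AUDIT-C:** the patient completes it on paper with the show-card at both time points. The baseline sheet is handed to the physician for scoring and feedback; the follow-up sheet is sealed. The mode of completion is then the same at both times.
3. **Analysis:** read effectiveness from the between-arm difference in change, not from within-arm change.

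**Cost:** printed sheets and envelopes, and no extra staff. Some items will be left blank, and physicians cannot query a sealed sheet. The physician still sees the baseline answers. Some self-report bias remains, because patients know what advice they received. The article does not state how patients are contacted at 3 months, so the sealed sheet assumes that they attend in person.

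**If self-completion is not workable**, keep physician recording, state the limitation, and draw no effectiveness conclusion from the within-arm AUDIT-C change.
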